| **Statistical analysis** | The statistical analysis plan will be developed after the protocol is finalized and will be finalized before database lock. The statistical analysis plan will specify and describe in detail all statistical analyses to be conducted based on the main features of the protocol. All statistical analyses will be computed using SAS statistical analysis software.  This study will provide statistical descriptions of all variables obtained at each observation time point, grouped by dose, unless the protocol specifies that statistical descriptions are not required at specific time points. Overall, continuous variables (such as age) will be statistically described using the number of observations, mean, median, standard deviation, minimum, and maximum; Categorical variables will be statistically described using the frequency and percentage of each category. The final analysis of the study will be based on data collected from subjects throughout the study period. Statistical methods will be detailed in the statistical analysis plan.  The results of this trial will primarily use descriptive statistical analysis. For continuous data, the mean, standard deviation, median, maximum, and minimum will be listed; for count data and ordinal data, the frequency (composition ratio), rate, and 95% confidence interval (CI) will be provided. Describe the number of subjects enrolled in each dose group, the cases of dropout and exclusion, and perform descriptive statistical analysis on the baseline characteristics of the enrolled cases.  **Evaluation of efficacy:**  **Primary efficacy endpoints:** Efficacy analysis is based on the number of subjects achieving the primary endpoint indicators after treatment.  The number of subjects, percentage, and 95% confidence interval for ORR are estimated using the Clopper-Pearson method.  **Secondary efficacy endpoints:** Efficacy analysis is based on the number of subjects achieving the secondary endpoint indicators after treatment.  The median and 95% confidence intervals for PFS, OS, TTP, and DOR are estimated using the Kaplan-Meier method (PROC LIFETEST), and survival curves are plotted.  DCR is summarized, including the number of subjects with DCR, percentage, and 95% confidence interval (calculated using the Clopper-Pearson method).  The comparison of pre- and post-treatment changes in ECOG PS score and AFP values will be conducted using paired t-test.  **Safety Evaluation:**  Descriptive statistical analysis will be primarily used to list and describe the adverse events (AEs) and adverse reactions that occurred in each dose group during this trial (where adverse reactions are defined as AEs that are 'definitely related, probably related, or possibly related to the investigational drug'). Laboratory test results will describe situations where values were normal before the trial but abnormal after treatment, as well as the relationship between these abnormal changes and the investigational drug. |

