# Study Population

## Inclusion criteria

Patients who meet all of the following criteria may be included in this study:

1. Voluntary enrollment with signed written informed consent;
2. Aged 18 to 80 years (inclusive), regardless of gender;
3. Patients with hepatocellular carcinoma clinically diagnosed according to the 'Guidelines for the Diagnosis and Treatment of Primary Liver Cancer (2019 Edition)' or confirmed by histological/cytological diagnosis;
4. Patients with unresectable or metastatic hepatocellular carcinoma;
5. No prior systemic treatment. Patients who have received adjuvant chemotherapy after local treatment may also be included if the chemotherapy ended more than 12 months ago and there has been disease progression or metastasis;
6. The last intervention, radiotherapy, and ablation treatment must have ended more than 4 weeks ago;
7. Patients who have previously undergone liver resection should have R0 resection, and tumor recurrence should occur more than 24 months after surgery;
8. There must be at least one assessable lesion (according to RECIST 1.1 criteria) ;
9. Expected survival time ≥ 3 months;
10. Eastern Cooperative Oncology Group (ECOG) performance status (PS) score of 0-1;
11. Child-Pugh score ≤ 7;
12. Able to cooperate in observing adverse events and efficacy;
13. Major organ functions are normal, meeting the following criteria:

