**Complete blood count (no blood transfusion or G-CSF use within 14 days prior to screening):**

1. Hemoglobin ≥ 90 g/L;
2. Absolute Neutrophil Count (ANC) ≥ 1.5×10^9^ /L;
3. Platelet count ≥ 75 × 10^9^ /L;

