**Biochemical tests (no albumin use within 14 days prior to screening):**

1. Albumin ≥ 28 g/L;
2. Total bilirubin ≤ 2 × upper limit of normal (ULN);
3. Aspartate aminotransferase (AST), alanine aminotransferase (ALT) ≤ 5 × ULN;

g) Alkaline Phosphatase (ALP) ≤ 5×ULN;

h) Creatinine ≤ 1.5×ULN;

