### Abnormal laboratory test values

Not every abnormal laboratory test value qualifies as an AE. Abnormal laboratory test results must be reported as AEs when they meet any of the following criteria:

- Accompanied by clinical symptoms;
- Leading to changes in study treatment (e.g., dose adjustment, treatment interruption, or termination of treatment);
- Requires medical intervention (e.g., potassium supplementation for hypokalemia) or changes in concomitant medication;
- The investigator considers it clinically significant.

If a clinically significant laboratory abnormality is a sign of a disease or syndrome (e.g., ALP and bilirubin > 5 ULN related to cholestasis), only the diagnosis (i.e., cholestasis) needs to be recorded on the AE page of the CRF.×

If a clinically significant laboratory test result abnormality is not indicative of a specific disease or syndrome, the abnormal result itself should be recorded on the AE page of the CRF, accompanied by a description indicating whether the result is above or below the normal range (e.g., 'hyperkalemia' instead of 'potassium abnormality'). If an abnormal laboratory test result is defined as per the standard and can be accurately described using a clinical term, that clinical term should be recorded as an AE. For example, if serum potassium rises to 7.0 mEq/L, it should be recorded as 'hyperkalemia.'

If the same clinically significant abnormal laboratory test result is observed between visits, it should only be counted once on the AE page of the CRF (for detailed information on recording persistent AEs, please refer to Section 8.8.4 ).

The investigator is responsible for reviewing all laboratory test results. For laboratory abnormalities that meet the criteria for adverse events, follow-up should continue until normalization or baseline levels are achieved and/or there is a reasonable and sufficient explanation.

Laboratory abnormalities that do not meet the definition of adverse events should not be reported as AEs. CTCAE graded events of grade 3 or 4 (severe) do not automatically qualify as SAEs unless they meet the definition of serious adverse events and/or are determined by the investigator to be serious adverse events.

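### The synopsis describes laboratory change as normal-to-abnormal, which cannot show worsening in patients who enter with abnormal liver tests or low platelets

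*Protocol*

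**What the plan says.** Four parts of the protocol bear on this.

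- **The laboratory rule.** The Safety Evaluation paragraph in the synopsis (Statistical analysis row) states: "Laboratory test results will describe situations where values were normal before the trial but abnormal after treatment". The same sentence adds a description of how these changes relate to the investigational drug. No other statement in the protocol says how a patient's laboratory values before and after treatment are to be compared in the analysis.
- **Eligibility.** Section 4.1 allows "Aspartate aminotransferase (AST), alanine aminotransferase (ALT) ≤ 5 × ULN", "Alkaline Phosphatase (ALP) ≤ 5×ULN", total bilirubin up to 2×ULN, albumin down to 28 g/L, "Platelet count ≥ 75 × 10^9^ /L" and "Child-Pugh score ≤ 7". Appendix Four places a score of 7 in Class B.
- **General description.** The same synopsis row says: "This study will provide statistical descriptions of all variables obtained at each observation time point, grouped by dose". Section 10 repeats the commitment without the dose grouping. Section 10.4 promises a descriptive table for all safety parameters, AEs summarised by CTCAE grade, and a safety evaluation that takes laboratory results into account. None of this is limited to patients with normal baselines.
- **When a laboratory change is an AE.** Section 8.8.5 says: "Not every abnormal laboratory test value qualifies as an AE". It requires symptoms, a change in study treatment, medical intervention, or the investigator's view that the abnormality is clinically significant. Section 8.1 is similar for laboratory deterioration.

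**The concern.** A normal-to-abnormal description suits a population that starts with normal values. This population has unresectable liver cancer, and the entry limits expressly allow liver tests above normal. A patient already above the limit for a test can never be counted under the synopsis sentence, however far the value rises.

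Safety is part of the secondary objective (section 2.2), and the regimen combines hepatic arterial chemotherapy, a kinase inhibitor and an anti-PD-1 antibody. Hepatic and platelet changes are therefore a main safety question. In the prospective triplet study cited in section 1.5, raised AST and thrombocytopenia were among the most common grade 3-4 treatment-related events, at 13.9% each. Patients who start with abnormal liver tests are those in whom further hepatic change most needs to be seen patient by patient.

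**Working it through.** There is no planned figure to reproduce. The check compares the passages, with one arithmetic illustration.

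**1. An eligible patient that the rule cannot count.**
- Entry: ALT 4×ULN, which is within the 5×ULN limit in section 4.1. On the scale in section 8.3.7 this is Grade 2 (above 3.0 to 5.0×ULN).
- On treatment: ALT 12×ULN, which is Grade 3 (above 5.0 to 20.0×ULN).
- Relative change: (12 − 4) / 4 = 200%.
- Synopsis rule: the value was abnormal before and abnormal after, so it is not a normal-to-abnormal change. The change and its relationship to the drug both fall outside that description.

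**2. The protocol recognises this kind of worsening elsewhere.** Table 1 in section 5.3 has a separate hepatitis criterion for patients whose AST, ALT or bilirubin was above ULN at baseline, based on a rise of at least 50%. The 200% rise in step 1 exceeds that. The analysis description has no counterpart.

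**3. Where such a patient still appears.**

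| Output | Includes an abnormal baseline? | Gives a patient-level count of worsening? |
| --- | --- | --- |
| Synopsis normal-to-abnormal description | No | Only from a normal baseline |
| By-visit statistics (synopsis, section 10) | Yes | No: mean, SD, median, minimum, maximum |
| Table of all safety parameters (section 10.4) | Yes | Not stated |
| AE tables (sections 8.1, 8.8.5, 10.4) | Yes, if the AE criteria are met | Yes, for recorded AEs |
| SAE reporting (section 8.8.7) | Yes, for raised ALT or AST with raised bilirubin or jaundice | Yes, for those cases |

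The remaining gap is worsening from an abnormal baseline that meets no AE criterion. It enters the by-visit aggregates, with no stated count by patient or grade. It also has no attribution, because the causality assessment in section 8.5 applies to AEs and the synopsis sentence covers only normal-to-abnormal changes.

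**4. How many patients the synopsis description could leave out.** The share with an abnormal baseline is not given, so a range is assumed for a single test, with the planned 30 patients:
- 20%: 0.20 × 30 = 6
- 80%: 0.80 × 30 = 24

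These are patients who could not contribute to that test's normal-to-abnormal description. They are not events lost from the safety report.

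**The case against.** The strongest reply is that the synopsis sentence excludes nothing. It says what will be described and does not say that nothing else will be. It stands beside a commitment to describe every variable at every time point, and section 10.4 covers all safety parameters. Marked deterioration would normally reach the AE tables as well: section 8.8.5 needs no normal baseline, acting on Table 1 for a patient with raised baseline values is a treatment change and so makes the abnormality an AE, and section 8.8.7 makes combined transaminase and bilirubin elevation an SAE. The detailed layout of tables also belongs to the statistical analysis plan, which is not shown.

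Most of this stands, and it rules out three stronger readings.

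- A reader might infer that patients with abnormal baselines disappear from the safety summary. They do not, as the table above shows.
- A reader might infer that the rule makes the combination look safer. The documents do not support this, because the AE tables and general summaries apply whatever the baseline.
- A reader might multiply the 13.9% in the cited study by an assumed share with abnormal baselines and call the result undescribed events. Those figures are treatment-related AEs. Comparable events recorded as AEs here would be tabulated under section 10.4.

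The reply does not remove the mismatch. The objection to the rule is not that a shift table has been left to the analysis plan. The protocol states one form of before-and-after laboratory description, and that form does not suit the patients it admits. The synopsis says the analysis plan will build on the main features of the protocol, so the narrower form may be carried forward.

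**Conclusion.** The point holds as a limited one. The synopsis rule for laboratory change and its attribution is poorly matched to the entry criteria and narrower than section 10.4. The consequence is the lack of a stated patient-level count, and of an attribution, for worsening from an abnormal baseline that does not meet the AE criteria in sections 8.1 and 8.8.5.

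The number of such changes cannot be derived from the protocol. The range of 6 to 24 of 30 patients per test rests wholly on the assumed 20% to 80%, and it measures who falls outside one description. The statistical analysis plan may already contain a suitable display; if so, only the synopsis wording needs to be brought into line. The change is worth making because it costs little and bears on hepatic safety, a main question for this regimen.

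**What to change.** Replace the synopsis sentence, and put the same text in section 10.4:

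*Laboratory results are presented for all treated patients as shifts from baseline CTCAE grade to worst post-baseline grade, with the number worsening by at least one grade and to grade 3-4, whatever the baseline value, and the relationship of these changes to the investigational drug; Child-Pugh score is shown as a shift from baseline to worst post-baseline score.*

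The cost is one sentence in two places and a few more standard tables. Appendix 1 already schedules blood counts and biochemistry at screening and from the second cycle onward, and section 6.3 already requires Child-Pugh every 3 weeks, so no visit or test is added. The synopsis already calls for the relationship to the drug to be described for normal-to-abnormal changes; the new wording extends that description to worsening from an abnormal baseline.

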
# Abbreviation List

| ACEI | Angiotensin-converting enzyme inhibitors |
| --- | --- |
| ADR | Drug adverse reactions |
| AE | adverse events |
| AFP | Alpha-fetoprotein |
| APTT | Activated Partial Thromboplastin Time |
| ALP | Alkaline Phosphatase |
| ALT | Alanine Aminotransferase |
| Ames | Mutagenicity Testing of Contaminants |
| ANC | Neutrophil Count |
| ARDS | Acute Respiratory Distress Syndrome |
| AST | Aspartate Aminotransferase |
| AT1 | Angiotensin II Receptor |
| AUC _0-t_ | Area Under the Concentration-Time Curve from the First Dose to the Set Time |
| AUC _0-t,ss_ | Area Under the Concentration-Time Curve from the Last Dose to the Set Time |
| AUCss | Area Under the Steady-State Concentration-Time Curve |
| Bid | Twice Daily |
| NMPA | National Medical Products Administration |
| NYHA | New York Heart Association |
| CHL | Chinese Hamster Lung Cells |
| CI | Confidence Interval |
| C _max_ | Peak Concentration |
| CR | Complete Remission |
| CRF | Case Report Form |
| CRO | Contract Research Organization |
| CT | Computed Tomography |
| CTCAE | Common Adverse Event Evaluation Criteria |
| CTL | Cytotoxic T Lymphocytes |
| CTLA-4 | Cytotoxic T Lymphocyte Antigen-4 |
| DCR | Disease control rate |
| DLT | Dose-Limiting Toxicity |
| dMMR | Mismatch Repair Deficiency |
| DOR | Duration of Response |
| EC | Ethics Committee |
| ECG | Electrocardiogram |
| ECOG | Eastern Oncology Cooperative Group |
| ERK | Extracellular Regulating Protein Kinase |
| FAAN | Food Allergies and Allergy Networks |
| FACT-Hep | Liver and Gallbladder Scale of the Cancer Treatment Function Evaluation System |
| FAS | Full Analysis Set |
| FDA | U.S. Food and Drug Administration |
| FDG-PET | Fluorodeoxyglucose Positron Emission Tomography |
| FT3 | Free Triiodothyronine |
| FT4 | Free Thyroxine |
| GCP | Good Clinical Practice for Drug Trials |
| G-CSF | Granulocyte Colony-Stimulating Factor |
| HAIC | Hepatic Arterial Infusion Chemotherapy |
| HBcAb | Hepatitis B Virus Core Antibody |
| HBeAb | Hepatitis B Virus e Antibody |
| HBeAg | Hepatitis B Virus e Antigen |
| HBsAb | Hepatitis B Virus Surface Antibody |
| HBsAg | Hepatitis B Virus Surface Antigen |
| HBV | Hepatitis B Virus |
| HCC | Hepatocellular Carcinoma |
| HCV | Hepatitis C Virus |
| HFSR | Hand-Foot Syndrome |
| HIV | Human Immunodeficiency Virus |
| HNSTD | Maximum Tolerated Dose |
| HR | Risk Ratio |
| IB | Investigator's Brochure |
| ICC | Intrahepatic Cholangiocarcinoma |
| ICF | Informed Consent Form |
| ICH | International Conference on Harmonization of Technical Requirements for Registration of Pharmaceuticals for Human Use |
| IFN | interferon |
| IL-6R | interleukin-6 receptor |
| IMRT | intensity-modulated radiotherapy |
| INR | international normalized ratio |
| irAE | immune-related adverse events |
| irRECIST | immune-related solid tumor efficacy evaluation criteria |
| JAK | Janus kinase |
| LVEF | left ventricular ejection fraction |
| MDSC | bone marrow-derived suppressor cells |
| MedDRA | International Medical Terminology Dictionary |
| MEK | mitogen-activated protein kinase |
| MRI | magnetic resonance imaging |
| MSI-H | microsatellite instability high |
| MTD | maximum tolerated dose |
| MVI | microvascular invasion |
| NIAID | National Institute of Allergy and Infectious Diseases |
| NOAEL | No adverse reaction dose level observed |
| NSAID | Non-steroidal anti-inflammatory drugs |
| ORR | Objective response rate |
| OS | Overall survival |
| PDGFR | Platelet-derived growth factor receptor |
| PD-1 | Programmed cell death receptor-1 |
| PD-L1 | Programmed cell death ligand-1 |
| PEF | Peak expiratory flow rate |
| PEG | Polyethylene glycol |
| PET | Positron emission tomography |
| PFS | Progression-free survival |
| PK | Pharmacokinetics |
| PPS | Protocol compliance |
| PR | Partial response |
| PS | Performance status |
| PT | Prothrombin time |
| PT | Preferred terminology |
| PVTT | Portal vein tumor thrombus |
| Qd | Once daily |
| Qod | Once every other day |
| Q3W | Once every 3 weeks |
| RECIST | Response Evaluation Criteria in Solid Tumors |
| RFS | Progression-free survival |
| SAE | serious adverse events |
| SBRT | Stereotactic radiotherapy |
| SD | Disease stability |
| SOC | System organ classification |
| SS | Safety analysis set |
| t _1/2_ | Elimination half-life |
| TACE | Transarterial chemoembolization |
| TEAE | Adverse events occurring during treatment |
| TKI | Tyrosine kinase inhibitors |
| T _max_ | Time to peak |
| TNF | Tumor necrosis factor |
| Treg | Regulatory T cells |
| TSH | Thyroid-stimulating hormone |
| T4 | Total Thyroxine |
| TT | Thrombin Time |
| TTP | Time to Disease Progression |
| TTR | Time to Tumor Recurrence |
| TTUP | Time to Unresectable Progression |
| ULN | Upper Limit of Normal Values |
| VEGF | Vascular Endothelial Growth Factor |
| VEGFR | Vascular Endothelial Growth Factor Receptor |

# Research Background

## Hepatocellular Carcinoma

Hepatocellular carcinoma (HCC) is one of the most common malignant tumors clinically worldwide, with over 700,000 new cases reported annually, ranking fifth among malignant tumors; Approximately 680,000 deaths per year, ranking third in cancer-related deaths, only behind lung cancer and gastric cancer ^[1]^. Globally, the incidence of hepatocellular carcinoma is also increasing year by year. 90% of primary liver cancer cases are hepatocellular carcinoma, which is a cancer with distinctive characteristics in China. In our country, liver cancer ranks 5th in incidence and 2nd in mortality among tumors, accounting for 55% of the global incidence and 45% of the global mortality each year. China is the country with the highest incidence and mortality of liver cancer in the world ^[2]^. Hepatocellular carcinoma is one of the malignant tumors that severely threaten the life and health of the people in our country.

Currently, surgical resection remains one of the most effective treatment methods for hepatocellular carcinoma. However, due to the lack of typical clinical manifestations in early-stage liver cancer, once symptoms and signs appear, the disease has often progressed to the middle or late stages. Most patients are unable to undergo radical surgical resection due to reasons such as high tumor burden, tumor metastasis, or the patient's physical condition or cardiopulmonary function being unable to withstand major traumatic surgery. Only 20% to 30% of patients meet the requirements for surgical treatment, and the recurrence rate of tumors after liver cancer resection is still very high, with a treatment effect that is not satisfactory; the 5-year recurrence rate reaches 60% to 70%, or even higher ^[3,4]^. Due to the complexity of tumor biological behavior in liver cancer and the limitations of various single treatment methods, the current consensus in the field of liver cancer treatment is a multidisciplinary collaboration and the coexistence of multiple treatment methods, which often involves a comprehensive approach in clinical practice that combines intervention, ablation, targeted therapy, immunotherapy, and radiochemotherapy to control tumor progression.

## Hepatic Arterial Infusion Chemotherapy (HAIC)

The liver receives dual blood supply from the hepatic artery and the portal vein, with 70% of the normal liver's blood supply coming from the portal vein and the remaining 30% from the hepatic artery, while the blood supply to liver cancer is primarily provided by the hepatic artery. Therefore, by administering through the hepatic artery, it is possible to maintain continuous exposure of the tumor to high concentrations of chemotherapeutic agents, maximizing the destruction of tumor cells while minimizing the impact on normal liver tissue. Additionally, due to the first-pass effect of the liver, the systemic dose of most chemotherapeutic agents is relatively low, resulting in reduced systemic toxic side effects. Hepatic Arterial Infusion Chemotherapy (HAIC) involves puncturing the right femoral artery (or other arteries such as the radial artery, subclavian artery, etc.), inserting a catheter, and performing angiography of the celiac trunk and mesenteric artery. Then, based on the arterial blood supply to the tumor, the catheter is selectively placed into the artery supplying the tumor. If the tumor receives blood supply from both the celiac trunk and the superior mesenteric artery simultaneously, or has other sources of supplying arteries, a microcatheter will be placed into the largest supplying artery of the tumor. Subsequently, chemotherapeutic agents will be pumped into the liver and tumor tissue for a prolonged and stable duration through the hepatic artery catheter. HAIC is routinely repeated every 3 weeks, with each session involving re-angiography, catheterization, and fixation; if there are changes in the tumor's blood supply, the catheter should be repositioned in the supplying vessel of the tumor each time. As one of the treatment strategies for interventional therapy, HAIC has undergone 30 years of development and is now commonly performed using the FOLFOX regimen for chemotherapy, with the technical aspects having become very mature ^[5-7]^.

Compared with TACE, HAIC can sustain administration for several days, significantly increasing the total dose of chemotherapeutic agents, prolonging the action time of high-concentration chemotherapeutic drugs, and avoiding the use of any embolic agents, thereby eliminating the occurrence of adverse events such as embolic syndrome and ectopic embolism, demonstrating better safety and efficacy, especially suitable for patients with portal vein tumor thrombus and large liver cancer, providing unresectable liver cancer patients with a higher objective tumor response rate and surgical conversion rate ^[8]^.

